## Abstract

**Background:**

California has the largest number of people living with HIV in the United States, and in 2022, there were 4882 new diagnoses. Veterans with histories of substance use, viral hepatitis, sexually transmitted infections, and homelessness carry substantial HIV burden. Testing is essential, yet approximately 12% of Californians with HIV were undiagnosed in 2020, and 50% of veterans in care had never been tested as of 2023. HIV self-tests (HIVSTs) can mitigate stigma, confidentiality, and access barriers, and vending machines (VMs) offer private, convenient distribution. However, the use of VM-dispensed HIVST has not been evaluated for veterans or within Veterans Affairs (VA) settings.

**Objective:**

We describe a Reach, Evaluation, Adoption, Implementation, and Maintenance–guided pre-implementation protocol to evaluate VM-dispensed HIVSTs in Northern California VA clinics and supportive housing settings.

**Methods:**

Fifteen VMs will stock oral-fluid HIVSTs (n=900). Program data (de-identified dispense logs), veteran electronic surveys (n=90), and qualitative interviews (n=15) will quantify reach (uptake), early effectiveness proxies (use, results, and next steps), adoption (machine/site dispensing), implementation (stockouts, restocking interval, and costs), and maintenance (dispensing trends).

**Results:**

Ethics approval activities (study material development and Institutional Review Board submission) began 2 months prior to the receipt of award funding (January to February 2025). Following funding, the project is planned for over a total of 18 months (12 months original project period + 6 months no-cost extension; March 2025 to August 2026). Ethics approval was obtained in August 2025. Veteran feedback was incorporated into study materials, and HIVSTs were purchased and packaged in September to November 2025. HIVSTs were added to VMs, and data collection is projected to occur from December 2025 through June 2026. Results are anticipated to be available in August 2026.

**Conclusions:**

This study will generate practice-ready evidence on the feasibility, acceptability, and early behavioral impacts of VM-dispensed HIVSTs for veterans. By pairing a stigma-responsive delivery channel with pragmatic measures, findings can inform equitable scale-up across VA and community settings, guide comparative evaluations of distribution channels (VMs, mail-to-home, or clinic pick-up), and support privacy-preserving linkage strategies to confirmatory testing, HIV pre-exposure prophylaxis, and treatment. Results will address a critical evidence gap for veteran-focused HIV prevention and provide parameters for multi-site evaluations.

## Introduction

San Francisco and Alameda Counties, core jurisdictions in the United States Ending the HIV Epidemic initiative, continue to experience concentrated HIV burden among populations served by the San Francisco Veterans Affairs Health Care System (SFVAHCS) [1]. Despite national recommendations for routine and risk-based screening, testing within Veterans Affairs (VA) care centers remains suboptimal, with many veterans never having been tested [2,3]. Addressing this persistent screening gap requires approaches that extend beyond traditional clinic workflows and that better reflect how veterans prefer to seek prevention services.

Multiple barriers impede routine testing in VA and community settings alike. Veterans report concerns about confidentiality and stigma, competing demands during clinical visits, uncertainty about eligibility or need for testing, and logistical hurdles such as travel and wait times [4]. Clinicians cite limited time, competing priorities, and variable comfort initiating testing discussions [5]. Framed through a behavioral lens, these barriers cluster around privacy, autonomy, convenience, and perceived control—constructs linked to testing avoidance and delayed diagnosis.

HIV self-tests (HIVSTs) are a recommended complement to facility-based testing and can mitigate several of these barriers by enabling private, user-directed testing [1,6-11]. Distributing HIVSTs through vending machines (VMs) further increases anonymity and convenience, while leveraging existing low-touch infrastructure. Early experience from non-VA settings suggests VM distribution is feasible and acceptable; however, its utility for veterans, and its implementation within VA facilities and partnered housing sites, have not been evaluated [12-16].

This protocol responds to this gap by describing a mixed-methods evaluation of VM-dispensed HIVSTs within the SFVAHCS and affiliated supportive housing locations. Guided by the Reach, Evaluation, Adoption, Implementation, and Maintenance (RE-AIM) framework, this study will characterize reach, adoption, and implementation at the site level and assess early individual-level behaviors related to test use [17]. By pairing a stigma-responsive delivery channel with pragmatic measures, this work aims to generate actionable evidence for VA and community partners considering VM-enabled HIV screening.

## Methods

### Study Aims and Objectives

This is a single-arm, mixed-methods pilot implementation evaluation that aims to evaluate the RE-AIM of VM-dispensed HIVSTs among Veterans located in Northern California (Table 1) [17].

**Table 1. T1:** Study aims and hypotheses.

Aim	Description	Hypothesis
Aim 1: Reach	Characterize HIV risk factors among veterans who obtained ≥1 VM^a^-dispensed HIVST^b^.	Among survey respondents, commonly reported HIV risk indicators will include male-to-male sexual contact, condomless sex, and unregulated drug use in the past 6 months.
Aim 2: Effectiveness (early outcomes; not causal)	Describe early, self-reported outcomes after obtaining a VM-dispensed HIVST (eg, intended use, completed use, results, and planned next steps) and the perceived usefulness of embedded HIV resources.	Most participants will report intending to use or having used the HIVST, will report reviewing the included post-test resources, and will report an intention to seek confirmatory testing and/or prevention services (eg, HIV pre-exposure prophylaxis).
Aim 3: Adoption	Identify which VM locations have the highest HIVST dispensing volume and when dispensing occurs (eg, clinic vs supportive housing; weekday vs after hours).	HIVST dispensing will be the highest at locations with higher baseline VM utilization and/or higher concentration of veterans experiencing housing instability (eg, supportive housing sites or outpatient clinics serving veterans experiencing homelessness).
Aim 4: Implementation and Maintenance	Assess implementation outcomes (eg, direct costs) and acceptability/experience of veterans with VM-dispensed HIVST (eg, convenience, privacy, satisfaction, and preference compared with other access points).	Participants will rate the VM delivery method as highly acceptable (eg, convenient, private, and satisfactory) and will describe VM access as a low-barrier, low-stigma option for obtaining HIV testing; dispensing will be feasible to maintain over the pilot period with measurable restocking workflows.

a VM: vending machine.

b HIVST: HIV self-test.

To accomplish this, we will collect veteran self-report data from 15 VMs via an electronic web-based Questionnaire 1 (n=90), a semi-structured qualitative interview paired with Questionnaire 2 (n=15), and HIVST distribution data (n=900) via the EMS software (VendNovation LLC). Our study lacks a comparison condition. Accordingly, the “effectiveness” outcomes are limited to early, self-reported behaviors and perceived usefulness/acceptability; causal inference regarding changes in HIV testing, diagnosis, or linkage to care is not possible.

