### Study Measures and Outcomes

Study measures and outcomes will be mapped onto the RE-AIM framework for evaluating individual and organizational factors that determine public health impacts of a program or policy (Table 2) [17].

**Table 2. T2:** Application of the RE-AIM^a^ framework to the proposed study.

Dimensions	Measures/Outcomes	Data source	Data level
Reach the target population	Number of participants who access ≥1 HIVST^b^	HRVM software (EMS, VendNovation LLC)	Organizational
	Participant demographics and characteristics, sexual partners and practices, drug use practices	Electronic Questionnaires 1 and 2	Individual
Effectiveness or efficacy	Participant HIVST usage plan, results, and steps after testing	Electronic Questionnaire 1	Individual
Adoption by target staff, settings, systems, and communities	Number of HIVSTs dispensed, location, date, and time	HRVM software (EMS, VendNovation LLC)	Organizational
Implementation consistency, costs, and adaptations made during delivery	Direct costs (vending machine coils and HIVSTs)	Purchase order invoices	Organizational
Maintenance/sustainment of intervention effects in individuals and settings over time	Participant reported outcome measures	Electronic Questionnaire 1; semi-structured qualitative interview	Individual

a RE-AIM: Reach, Evaluation, Adoption, Implementation, and Maintenance.

b HIVST: HIV self-test.

The RE-AIM framework has been utilized in similar studies evaluating health care provider views on HIVSTs, workplace HIV testing, integrating HIV prevention services into family planning, barriers and facilitators to HIV pre-exposure prophylaxis uptake, and provision of conditional financial incentives to people living with HIV [18-22].

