### Sample Size and Precision

This pilot implementation evaluation is designed to estimate feasibility and acceptability outcomes rather than to test efficacy. Funding was allocated for the purchase of 900 HIVSTs. Assuming 100% distribution during the data collection period, we estimated a ~10% optional survey response rate based on a similar HIVST distribution study and targeted up to 90 completed surveys [16]. With 90 survey responses, descriptive estimates of key feasibility/acceptability proportions (eg, intended/actual test use, satisfaction, and perceived privacy) will have acceptable precision (eg, for proportions near 50%, an approximate 95% CI half-width of ~10 percentage points). We will conduct up to 15 qualitative interviews, which is expected to be sufficient to achieve thematic saturation for a focused inquiry on acceptability, barriers/facilitators, and implementation experiences.

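### Dispensing volume (Aim 3) and the dispensing trend are capped counts wherever the 900 tests run short; report them per in-stock machine-day as well

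*Protocol article*

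**What the plan says.** In the protocol article, Table 1 (Study Aims and Objectives) gives Aim 3 as "Identify which VM locations have the highest HIVST dispensing volume and when dispensing occurs". Its hypothesis is that "HIVST dispensing will be the highest at locations with higher baseline VM utilization and/or higher concentration of veterans experiencing housing instability". Table 2 (Study Measures and Outcomes) measures adoption as "Number of HIVSTs dispensed, location, date, and time", taken from the vending software.

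The abstract and Table 2 differ on the next two dimensions. The abstract has "implementation (stockouts, restocking interval, and costs), and maintenance (dispensing trends". Table 2 lists only "Direct costs (vending machine coils and HIVSTs" under implementation, and "Participant reported outcome measures" under maintenance. The Aim 4 hypothesis in Table 1 does expect restocking work to be measurable and dispensing to be sustainable over the pilot.

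Supply is set by funding at 900 tests. Sample Size and Precision derives the survey target by "Assuming 100% distribution during the data collection period", and Study Aims and Objectives likewise gives n=900 for the distribution data. Data Analysis says that organizational-level data will be described. No section relates volume or trend to in-stock time or to the stock loaded.

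**The concern.** A count drawn from a limited stock measures demand only while stock is available. If every test is dispensed, which is what the survey target supposes, total volume equals the number bought. Each machine's total may then say as much about how it was filled as about how much it was wanted. A count over calendar time has the same weakness: it drops to zero when stock ends, whatever users would have taken.

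The results are meant to inform scale-up and to supply parameters for multi-site work. A site ranking flattened by equal allocation, or a decline caused by exhaustion, would be a poor basis for either.

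**Working it through.** **Inputs from the article.** 900 tests; 15 machines (2 medical center, 7 clinic, 6 supportive housing); data collection December 2025 to June 2026, which is 7 months or 212 days; 100% distribution; about 10% survey response; 90 surveys.

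**The plan's own figures.** 900 × 1.00 × 0.10 = 90 surveys. The 95% half-width at 50% is 1.96 × √(0.25/90) = 10.3 points. Both reproduce, so full distribution does underlie the target.

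**Supply.** 900/15 = 60 tests per machine on average; 60/7 = 8.6 per machine-month. System-wide, supply runs short if demand exceeds 900/7 = 128.6 tests a month.

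**Trend, with constant demand assumed and perfectly shared stock.**
- 100 a month: 100 × 7 = 700, no exhaustion.
- 150 a month: 900/150 = 6.0 months.
- 200 a month: 900/200 = 4.5 months, so the last 2.5 months show zero.
- 300 a month: 900/300 = 3.0 months.

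At 200 a month, the first 3.5 months dispense 700 and the second 3.5 months dispense 200. The late-to-early ratio is 200/700 = 0.29 although the true ratio is 1.0. Per in-stock month the figures are 700/3.5 = 200 and 200/1.0 = 200, and the ratio returns to 1.0.

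**Ranking, with 60 tests fixed per machine and demands of 10 and 30 a month assumed.** The totals are min(60, 70) = 60 and min(60, 210) = 60, a ratio of 1.0 against a true 3.0. In-stock time is 6 and 2 months, so the rates are 60/6 = 10 and 60/2 = 30.

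The same pair shows why the trend must be taken within machines. In months 1 and 2 the pooled rate is (10 + 30)/2 = 20 per in-stock machine-month. In months 3 to 6 only the slow machine has stock and the pooled rate is 10. That is a false decline caused by the change in which machines contribute.

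**Simulation over a range of demand.** Assumptions, none of them given in the article: Poisson demand constant over 212 days, between-machine coefficient of variation 0.7, and 300 runs per cell. There are three supply rules: 60 per machine with no reallocation; a shared pool of 900 with refill to 15 every 30 days; and the same pool refilled every 7 days. Each cell shows the Spearman correlation of raw volume with true demand / share of runs with a tie for the highest total / late-to-early ratio (truth about 1.0). The last column is the correlation with true demand of dispenses per in-stock day.

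| Total demand | Fixed 60 | Pool, 30 days | Pool, 7 days | In-stock rate |
|---|---|---|---|---|
| 300 | 0.92 / 3% / 0.98 | 0.92 / 4% / 1.01 | 0.92 / 2% / 1.01 | 0.92 |
| 600 | 0.95 / 94% / 0.78 | 0.95 / 3% / 0.99 | 0.95 / 1% / 0.99 | 0.95 |
| 900 | 0.93 / 100% / 0.54 | 0.96 / 8% / 0.93 | 0.96 / 3% / 0.85 | 0.96 |
| 1350 | 0.83 / 100% / 0.33 | 0.92 / 46% / 0.60 | 0.96 / 1% / 0.32 | 0.96–0.97 |
| 1800 | 0.73 / 100% / 0.23 | 0.86 / 75% / 0.40 | 0.95 / 3% / 0.07 | 0.96–0.97 |
| 2700 | 0.58 / 100% / 0.12 | 0.65 / 90% / 0.21 | 0.95 / 2% / 0.01 | 0.97 |

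With fixed allocation, all 15 totals were equal in 3 of 300 runs at 1800 and in 28 of 300 at 2700. Those runs have no correlation and are left out of the average.

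**The case against.** Several points on the other side are sound.

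- The 100% figure is a planning assumption for the survey target, not a rule for running the machines. Uptake may fall well short of 900, and at a demand of 300 the table shows no distortion under any rule. This stands.
- Restocking is foreseen. If emptier machines are refilled more often, totals carry demand information: with weekly refills the raw ranking stays at 0.95 to 0.96 even at three times supply. This stands for the ranking. It does not rescue the trend, which reads 0.07 at a demand of 1800 under the same rule.
- The abstract promises stockouts and restocking intervals, and the log is time-stamped, so an attentive analyst could recognise exhaustion. This is true, and it is why the fix is cheap. But those data are not tied to the volume or trend measure, and Table 2 omits them.
- The article is condensed, and a fuller document may hold the restocking rule and the handling of out-of-stock time. The absence of a restocking rule is therefore not the point. The point is the outcome as stated, which is a count.
- Aim 3 can be read as an operational question that volume answers. That is a reason to keep raw volume, not a reason to report it alone.

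A reader might also object to the two-part hypothesis, because either a busy site or a housing site would confirm it, and might want volume divided by general machine traffic. The hypothesis names baseline utilization as a predictor and does not claim to separate traffic from demand for tests. In a descriptive pilot, splitting it is a matter of preference.

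**Conclusion.** The point holds in a conditional form. Where supply binds, volume by machine and the dispensing trend are capped counts, and the article ties neither to in-stock time. The trend is the more fragile: at an assumed 200 tests a month, flat demand gives a late-to-early ratio of 0.29. In the simulation the ratio is 0.60 or lower under every supply rule at a total demand of 1350 or more. The ranking suffers mainly when stock is fixed per machine or refilled slowly.

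A reader might infer that volume reflects stocking instead of demand. The article does not support that. It would be fully true only with a fixed allocation per machine and complete exhaustion, and the article states no such allocation. Nor can it be said that maintenance as a whole rests on the dispensing trend: only the abstract says so, while Table 2 uses participant-reported outcomes. All demand levels and supply rules used here are assumptions.

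**What to change.** 1. For Aim 3 and the dispensing trend, report tests dispensed per in-stock machine-day alongside raw volume. Use the time-stamped log with the stockout and restocking data promised in the abstract. Compute the trend within machines before summarising, so that machines dropping out do not create a decline.
2. Report, for each machine, the stock loaded and the dates on which it was empty. Treat time after exhaustion as unobserved, not as zero dispensing.
3. Add stockouts and restocking interval to the implementation row of Table 2.
4. Reconcile the maintenance measure between the abstract (dispensing trends) and Table 2 (participant-reported outcomes), naming both if both are meant.

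Denominators of registered users, other-product transactions or accessible hours are optional, if such data exist by machine; the article does not show that they do.

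The cost is a little extra analysis, some table wording, and the keeping of per-machine stock records through June 2026. Nothing more is asked of participants.

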### Timeline

The study is expected to be completed over 20 months (reflecting 2 months of pre-funding activities, 12 months for the original project period, and a requested 6-month no-cost extension). During months 1‐2 (January to February 2025), research team members designed initial study materials and submitted Institutional Review Board (IRB) protocols for review. During months 3‐8 (March to August 2025), requested edits to IRB protocols were incorporated, and IRB approval was attained. During months 9‐11 (September to November 2025), veteran feedback was obtained about the study materials, which were further refined and finalized; HIVSTs and VM coils were purchased; and HIVSTs were packaged with the study materials. HIVSTs were added to the VMs in December 2025. Data collection is projected to occur in months 12‐18 (December 2025 to June 2026), and data analysis is anticipated to be performed in months 19‐20 (July to August 2026).

### Setting

This study will be conducted at the SFVAHCS, which serves over 310,000 US Veterans at the San Francisco VA Medical Center and 9 community-based outpatient clinics located in Downtown San Francisco, Oakland, San Bruno, Santa Rosa, Clearlake, Ukiah, and Eureka, California. HIVSTs will be stocked in pre-existing SFVAHCS VMs: 2 are located at the San Francisco VA Medical Center, 7 in community-based outpatient clinics (all the cities listed above except San Bruno), and 6 in supportive housing buildings where veterans live (San Francisco and Daly City, California). Research study team members will conduct qualitative interviews with veterans at the San Francisco VA Medical Center and supportive housing buildings. The research study team will also be available via telephone and video to assist with recruitment, enrollment, and collection of study measures.

### Participant Eligibility and Recruitment

To be eligible for Questionnaire 1, participants must be a US Veteran (of any service discharge status), must be registered for VM access, and must have taken a HIVST from one of the 15 SFVAHCS VMs. To be eligible for the qualitative interview and Questionnaire 2, veterans must meet the eligibility criteria for Questionnaire 1 and must have personally used a VM-dispensed HIVST. Non-veterans who obtain a VM-dispensed HIVST from a veteran will be ineligible. Recruitment fliers will be taped on the VMs, HIVSTs, and posted in common areas of supportive housing buildings. The research team will attend veteran community meetings at supportive housing buildings to introduce the study and recruit participants.

### Ethical Considerations

We obtained approval by the University of California IRB and the San Francisco Veterans Affairs Human Subjects Committee in August 2025 (No. 25-43931). The research study team will obtain electronic or written informed consent before beginning the study questionnaire and qualitative interview. Participants will receive a US $20 electronic gift card after completion of Questionnaire 1 (maximum of US $40 per participant). Veterans who completed Questionnaire 2 would receive a US $100 gift card. Each veteran advocate will receive a US $1000 honorarium for their time and expertise (about 5 hours of work). HIVST dispensing data will be de-identified and tracked regularly throughout the study using HRVM software. All participant data collected will be de-identified to ensure privacy and confidentiality.

### Study Measures and Outcomes

Study measures and outcomes will be mapped onto the RE-AIM framework for evaluating individual and organizational factors that determine public health impacts of a program or policy (Table 2) [17].

**Table 2. T2:** Application of the RE-AIM^a^ framework to the proposed study.

Dimensions	Measures/Outcomes	Data source	Data level
Reach the target population	Number of participants who access ≥1 HIVST^b^	HRVM software (EMS, VendNovation LLC)	Organizational
	Participant demographics and characteristics, sexual partners and practices, drug use practices	Electronic Questionnaires 1 and 2	Individual
Effectiveness or efficacy	Participant HIVST usage plan, results, and steps after testing	Electronic Questionnaire 1	Individual
Adoption by target staff, settings, systems, and communities	Number of HIVSTs dispensed, location, date, and time	HRVM software (EMS, VendNovation LLC)	Organizational
Implementation consistency, costs, and adaptations made during delivery	Direct costs (vending machine coils and HIVSTs)	Purchase order invoices	Organizational
Maintenance/sustainment of intervention effects in individuals and settings over time	Participant reported outcome measures	Electronic Questionnaire 1; semi-structured qualitative interview	Individual

a RE-AIM: Reach, Evaluation, Adoption, Implementation, and Maintenance.

b HIVST: HIV self-test.

The RE-AIM framework has been utilized in similar studies evaluating health care provider views on HIVSTs, workplace HIV testing, integrating HIV prevention services into family planning, barriers and facilitators to HIV pre-exposure prophylaxis uptake, and provision of conditional financial incentives to people living with HIV [18-22].

